### Data Collection and Procedures

The first contact will be made *via* phone call by the research team, for those who declare an interest, the objective of the study and how it will be conducted will be explained (need to use a cell phone, data collection through an online form, intervention through videos and guidance), as well as the importance of adhering to the program. After verbal agreement to participate, a link will be sent by phone or messaging app, to sign the free and informed consent form and complete the baseline evaluation form, along with an explanatory video with information for possible doubts. Participants will perform the baseline assessment within a 2-week period before the start of the intervention. Support will be offered to the participants, to minimize the limitation of poor technology skills. In Figure 2 it is possible to observe the steps of the protocol.

**FIGURE 2 F2:**
[figure not shown]
Data collection procedures and steps.

The researchers responsible for delivering and assisting with the assessments will not know which group the individual is randomized to, that is, different researchers will have to send the informative videos and collect the weekly information about the exercises.

### Experimental Group

The PE will be carried out by the participants in a home-based format and all contact will be made by phone or messaging app. After the baseline assessment, the intervention will start and after 4 weeks of training, a post-intervention evaluation will be carried out, following the same procedure: link to the online form, accompanied by an explanatory video. Fifteen days after completion of the PE program, a follow-up assessment will be carried out. All participants will be able to contact the researchers in case of doubts regarding data collection and intervention. The importance of maintaining their routine medication use will be highlighted.

#### Intervention: Physical Exercise Protocol

The PE protocol was specifically developed to be performed by older individuals remotely in their homes, under the supervision of physical education professionals and physiotherapists. Physical Education Professionals and Physiotherapists are researchers experienced with prescribing and supervising RT for the elderly population. Supervision will be performed through explanatory videos, text messages, and, when necessary, by phone call. Professionals will be available for possible queries, *via* messaging application and call or e-mail.

Once a week, videos will be sent to the intervention group in the messaging application. The videos will contain exercises demonstrated by a professional and detailed explanations through audio and subtitles. To reinforce the performance of the PE, two messages will be sent per week to reinforce the practice instructions.

The dosage of the intervention will consist of 3 weekly sessions lasting 40–70 min each, with a 1-day break between them, for 4 weeks, totaling 12 sessions. The 4-week intervention will be divided into three periods to facilitate exercise progression; the first week (period 1) will be for adaptation and familiarization, and the second week (period 2), and third and fourth weeks (period 3) for the progression of repetitions and sets, as explained in Table 2 (Bird et al., 2005). The sessions will consist of exercises with free weights, strengthening exercises, and stretching. By performing at least 50–60 min in three sessions per week, older adults can reach the level of physical activity recommended by the WHO (World Health Organization [WHO], 2011) of 150 min per week.

**TABLE 2 T2:** Home physical exercise protocol for older adults during the COVID-19 pandemic.

Intervention weeks	Weekly frequency	Intensity	Volume*	Number of series	Speed in concentric and eccentric phase	Duration of each session
1°Week	3x	10 Repetitions	90	1	≈3 Segundos	36 min
2°Week	3x	10 Repetitions	180	2	≈3 Segundos	51 min
3°Week	3x	15 Repetitions	270	2	≈3 Segundos	1 h–1:06 min
4°Week	3x	15 Repetitions	270	2	≈3 Segundos	1 h–1:06 min

**The volume was calculated by multiplying the number of exercises, series and repetitions (Bird et al., 2005).*

The session will start with a 10-min warm-up consisting of rotation exercises for the upper and lower limb joints. Next, 30–40 min of muscle strengthening exercises will be performed, where the load will be the body weight and 500 ml water bottles (equivalent to 500 g), ending with 10 min of stretching. There will be no rest intervals between exercises due to the low intensity and volume.

During the sessions, the main muscle groups involved in the exercises will be the pectoralis major, latissimus dorsi, biceps brachii, triceps brachii, deltoids, glutes, quadriceps, hamstrings, and calves. The following exercises will be performed: Sit and stand up from a chair, bench press, unilateral row, knee flexion and extension, elbow flexion, lateral raise, plantar flexion, and abdominal contraction. The older adults will only perform the exercises applied in the study. A detailed description of the exercise protocol for each week can be found in Supplementary File 1.

As this is an older population, there is a need to maintain effective communication to reduce risk and promote greater safety among participants. For this reason, participants will be instructed and encouraged to perform their movements within available ranges, respecting their limits, using a chair support, and remaining comfortable. Through the informative videos, it will be explained in a simple way how they might feel during the exercise and what is the acceptable level of tiredness. Weekly contact will also be made to track possible difficulties, doubts, and adverse effects, such as pain, discomfort, fatigue, or dizziness, for example. If there are adverse effects, corrections will be investigated and made, however, without prejudice to the objective of the exercise. In addition, through the initial assessment it will be possible to analyze the health profile of the participants, which makes it possible to advance corrections for each one, if necessary.

To access and evaluate adherence, during the weekly contact, mentioned previously, the researcher will ask to confirm that they have completed the proposed exercises and the corresponding performed date. To ensure that the proposed intervention was performed indeed, the participants must also keep a diary, reporting the number of sets of each exercise and the duration of each session, this information will be collected by the researcher who will contact the participants (Lambert et al., 2017; Vitale et al., 2020).

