### Outcome Measures

The evaluations will be carried out before the beginning of the intervention, after 4 weeks of the intervention, and 15 days after the end of the intervention. In the initial assessment, a characterization questionnaire will be applied to obtain socioeconomic and health information.

The primary outcome will be the variable depression (Gorenstein and Andrade, 1996) and the secondary outcomes will be mood (Rohlfs et al., 2008), stress (Luft et al., 2007), sleep quality (Buysse et al., 1989; Bertolazi et al., 2009), quality of life (Power et al., 2005), anxiety (Beck et al., 1988) and physical abilities (Hlatky et al., 1989) of the older adults. The analyzed variables and the respective instruments are listed below in Table 1.

**TABLE 1 T1:** List of variables, instruments used, interpretation and reference.

Variables	Instruments	Interpretation of instruments/cutoff points	Authors (year)/articles
Depressive symptoms	BDI	These ups and downs are considered normal (1–10)/Mild mood disturbance (11–16)/Borderline clinical depression (17–20)/Moderate depression (21–30)/Severe depression (31–40)/Extreme depression (Over 40)	Gorenstein and Andrade (1996)/Validation of a Portuguese version of the BDI and State-Trait anxiety inventory in Brazilian subjects
Sleep quality	PSQI	Good sleep (0–4)/Sleep Disorder (5 or more)	Buysse et al. (1989)/The PSQI: a new instrument for psychiatric practice and research.
	Ese-Br	Scores above 10 suggest the diagnosis of excessive daytime sleepiness	Bertolazi et al. (2009)/Portuguese-language version of the Epworth sleepiness scale: validation for use in Brazil
Quality of life	WHOQOL—OLD	Need to improve (1–2.9)/Regular (3–3.9)/Good (4–4.9)/Very good (5)	Power et al. (2005). Development of the WHOQOL-old module
Stress	PSS	Scores can range from 0 to 56/Not the cut-off point.	Luft et al. (2007). Brazilian version of the Perceived Stress Scale: Translation and validation for the elderly
Mood states	BRUMS	Score can vary from 0 to 16/Not the cut-off point.	Rohlfs et al. (2008). BRUMS: an instrument for early detection of overtraining syndrome.
Anxiety	BAI	Scores between (0–21) indicates very low anxiety/(22–35) indicates moderate anxiety/A grand sum that exceeds 36 is a potential cause for concern.	Beck et al. (1988). An inventory for measuring clinical anxiety: Psychometric properties.

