### Adverse Events

Any adverse effects observed or reported by patients will be recorded and considered in the study results. In addition, these patients will be referred to medical care for proper treatment.

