### Control Group

To participants allocated to the control group a link will be sent to sign the free and informed consent form and complete the baseline evaluation form, along with an explanation video with information on possible doubts. The participants will also be asked to maintain their normal activities (including taking medications) and not to perform PE. After a period of 4 weeks, a link with an online form and an explanatory video for evaluation will be sent again. Fifteen days after this evaluation, the follow-up form and video will be sent. After the research period, a new invitation to carry out the proposed physical exercise program will be extended to the participants of the voluntary control group.

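### As described, only the exercise arm is asked about adverse effects on a schedule, so any between-arm account of harms would be biased by unequal ascertainment

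*Protocol article*

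**What the plan says.** **Exercise arm** (Intervention: Physical Exercise Protocol). Three kinds of contact are scheduled over the 4 weeks:

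- A video: "Once a week, videos will be sent to the intervention group in the messaging application".
- Reminders: "two messages will be sent per week to reinforce the practice instructions".
- A researcher check-in: "Weekly contact will also be made to track possible difficulties, doubts, and adverse effects". The text names pain, discomfort, fatigue and dizziness as examples. The same check-in serves adherence, since in it "the researcher will ask to confirm that they have completed the proposed exercises and the corresponding performed date".

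**Control arm** (Control Group). After the baseline form, "The participants will also be asked to maintain their normal activities (including taking medications) and not to perform PE". The next scheduled event is the post-intervention form: "After a period of 4 weeks, a link with an online form and an explanatory video for evaluation will be sent again". A follow-up form comes 15 days later. Nothing else is scheduled in between.

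**Both arms.** The Adverse Events section gives a general rule: "Any adverse effects observed or reported by patients will be recorded and considered in the study results". Under Outcome Measures, "The primary outcome will be the variable depression". Table 1 lists the instruments, and none of them is an adverse-effect checklist. Study Design says that the control group will be monitored, without saying how or how often. The limitations in the Discussion cover access to technology, self-reported attendance and unblinded participants. They do not mention unequal contact.

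**The concern.** Asking people about symptoms at set times usually yields more reports than waiting for them to volunteer. The weekly prompts name complaints that older people also have without exercising. If one arm is prompted every week and the other is not, a difference in recorded adverse effects can arise with no difference in what happened. The Adverse Events section says that these records will be considered in the results, so the imbalance can reach the report. Analysis cannot repair it later, because events that were never elicited are not in the data.

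A related question of interpretation concerns depression. The participants are socially isolated, the primary outcome is self-reported depressive symptoms, and the Introduction names isolation as a risk factor for depression. One arm has regular researcher contact and the other does not. A between-arm difference therefore belongs to exercise and contact together, and a conclusion that names exercise alone would say more than the design can show.

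**Working it through.** The plan gives no figure on this point to reproduce. The check is a count from the text, followed by two illustrations on stated assumptions.

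**1. Scheduled contacts between baseline and the 4-week form**

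| | Exercise | Control |
|---|---|---|
| Videos | 1 × 4 = 4 | 0 described |
| Reminder messages | 2 × 4 = 8 | 0 described |
| Researcher check-ins | 1 × 4 = 4 | 0 described |
| Total | 16 | 0 described |
| Of which ask about adverse effects | 4 | 0 described |

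Of the 16, the videos and messages (4 + 8 = 12) are sent out with no exchange described. The scheduled two-way contact is the 4 check-ins. For harms, the relevant contrast is 4 enquiries against none described.

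**2. Does the check-in extend to controls?** The sentence stands in the intervention section, and the check-in is used to confirm that the exercises were done and to collect the exercise diary. Neither applies to a control participant. The Control Group section sets out that arm's sequence and contains no such step.

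**3. What unequal capture does to a comparison of harms.** Let the true proportion with an adverse effect be p in both arms, with capture c₁ in the exercise arm and c₀ in controls.

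Apparent risk ratio = (p × c₁) / (p × c₀) = c₁ / c₀

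The value of p cancels. With c₁ = 1 (assumed):

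- c₀ = 0.75 gives 1 / 0.75 = 1.33
- c₀ = 0.50 gives 1 / 0.50 = 2.0
- c₀ = 0.25 gives 1 / 0.25 = 4.0

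In counts, recruitment is 56 + 12 = 68, or 34 per arm. Taking p = 0.30 (assumed) and ignoring dropout, the exercise arm would record 34 × 0.30 = 10.2 people. Controls at 50% capture would record 10.2 × 0.50 = 5.1. The capture fractions and the 30% are assumptions, and the documents give no value for either.

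**4. What contact alone could do to the depression comparison.** Suppose that exercise has no effect and contact has a standardised effect d (assumed). Take a two-sample t-test at two-sided 0.05 with 28 per arm (56 / 2), so 54 degrees of freedom and noncentrality d × √(28/2). This is a simpler test than the planned repeated-measures ANOVA. The chance of a significant result favouring the exercise arm is about 11% for d = 0.2, 20% for d = 0.3, 31% for d = 0.4 and 45% for d = 0.5. Nothing in the documents says which d is realistic, or that it differs from zero. If the claim is about the whole remote programme, such a result is not false. It is wrong only if credited to exercise alone.

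**The case against.** **Silence in a condensed article.** The article does not show the full content of the 4-week and 15-day forms, and it says that controls will be monitored. The adverse-event rule is not limited to one arm, and the Experimental Group section says that all participants may contact the researchers. A reader might infer that controls are never asked about adverse effects. The documents do not support that: they show only that no scheduled enquiry is described for controls. This limits the wording but leaves the point standing, because the article itself fixes a solicitation schedule in one arm and only a passive rule overall. Contact started by the participant to resolve doubts is not solicitation.

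**No comparison of harms is planned.** Adverse effects are not listed as an outcome and no between-arm test of them is specified. The weekly question has a safety purpose. This is correct, and the bias therefore applies to any descriptive comparison of adverse effects, not to a planned test.

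**A package against usual routine is a legitimate contrast.** The hypothesis refers to a remote protocol, the intervention section builds videos, messages and supervision into it, and the Discussion describes remote monitoring as part of it. A reader might infer that the depression comparison is invalid, or that the hypothesis credits exercise alone. Neither follows. What remains is a matter of wording, plus a limitation that the Discussion omits.

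**The contact is modest.** A reader might take the 16 contacts as sustained human interaction. Twelve are one-way, and the documents offer no evidence that four check-ins shift depression scores. Nor does the Introduction call lack of connection a cause of depression. It calls isolation a risk factor. These objections stand.

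**Conclusion.** The point holds for harms. As described, adverse effects are asked about four times in the exercise arm before the 4-week form and on no described occasion in controls. Any between-arm description would be biased against exercise, provided that asking finds more than waiting does. The size cannot be derived from the documents. An apparent risk ratio of 2 follows only if true rates are equal, capture is complete in the exercise arm and capture is 50% in controls. A reader might take a two- or three-fold false excess as an established figure, but it depends entirely on assumed capture.

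For depression the conclusion is narrower. The comparison is valid as a remotely supported exercise programme against usual routine. It cannot separate exercise from contact, and the report should say so. The sample size is unaffected.

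**What to change.** 1. Add one identical adverse-effect checklist to the 4-week and 15-day online forms of both arms, and use only that for between-arm reporting.
2. Keep the weekly exercise-arm reports as safety monitoring and present them separately, without a control column.
3. State what the monitoring of controls mentioned under Study Design consists of.
4. Word the conclusion on depression as the effect of exercise plus remote contact against usual routine, and add unequal contact to the limitations in the Discussion.

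The cost is a few form items and a few sentences. The downside is recall error over 4 weeks. The checklist also reduces the imbalance without removing it fully, since participants questioned weekly may remember more.

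Weekly check-ins for controls, about 34 × 4 = 136 contacts, are optional. They would turn a usual-routine control into an attention control, change the question being asked and possibly shrink the difference, so they are a trade-off for the sponsor to weigh.

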### Control Group

To participants allocated to the control group a link will be sent to sign the free and informed consent form and complete the baseline evaluation form, along with an explanation video with information on possible doubts. The participants will also be asked to maintain their normal activities (including taking medications) and not to perform PE. After a period of 4 weeks, a link with an online form and an explanatory video for evaluation will be sent again. Fifteen days after this evaluation, the follow-up form and video will be sent. After the research period, a new invitation to carry out the proposed physical exercise program will be extended to the participants of the voluntary control group.

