### Participants

The sample will be selected probabilistically with individuals aged 60 years and over from the city of Itajaí (Santa Catarina, Brazil). They will be recruited from a telephone directory of people registered with the Municipal Secretariat for the Promotion of Citizenship. Participants who meet the inclusion criteria will be randomized equally between two groups; the experimental group who will carry out the PE protocol (PEP) and the control group (CG) who will be instructed not to perform any type of PE and to follow their usual daily routines. For group allocation, patients will be randomized with a 1:1 computer-generated allocation^1^ and the researcher responsible for the randomization will not be involved in the evaluations.

To participate in the study, the following inclusion criteria will be respected: individuals of both sexes, aged ≥ 60 years (no maximum age limit); with internet access; able to understand and use the smartphone; with the physical and cognitive ability to understand and perform the exercises safely. The exclusion criteria will consist of elderly people who performed physical activity and/or exercise in the last 3 months, according to the criteria recommended by the World Health Organization (World Health Organization [WHO], 2011) (walks of 150 min per week and/or resistance training with weight for 75–150 min) and elderly people with any condition physical or cognitive that makes it impossible to practice the proposed exercises at home.

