### Ethics and Dissemination

The project was approved by the Ethics Committee for Research with Human Beings of the State University of Santa Catarina, under Certificate of Presentation of Ethical Appreciation (CAEE number) 40392220.2.0000.0118, approval number 4.617.650. The status of approval can be consulted on the website https://plataformabrasil.saude.gov.br. Written informed consent will be obtained from each respondent before data collection.

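### The Control Group section reads as consent and baseline after allocation, and no other section places them before randomisation

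*Protocol article*

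**What the plan says.** All places are in the protocol article.

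- **Control Group.** The section opens with this step: "participants allocated to the control group a link will be sent to sign the free and informed consent form and complete the baseline evaluation". A later sentence adds: "The participants will also be asked to maintain their normal activities (including taking medications) and not to perform PE".
- **Data Collection and Procedures.** One step is described for everybody: "After verbal agreement to participate, a link will be sent by phone or messaging app, to sign the free and informed consent form", together with the baseline form. No arm is named. Baseline is timed against the intervention, not against allocation: "Participants will perform the baseline assessment within a 2-week period before the start of the intervention".
- **Participants.** "Participants who meet the inclusion criteria will be randomized equally between two groups". Randomisation is linked to eligibility; consent and baseline are not mentioned as conditions. The researcher who randomises takes no part in the evaluations.
- **Experimental Group.** Baseline comes before training starts. No consent or baseline link after allocation is described for this arm.
- **Ethics and Dissemination.** "Written informed consent will be obtained from each respondent before data collection". This orders consent against data collection, not against allocation.
- **Masking.** Researchers who deliver assessments are kept unaware of the group (Data Collection and Procedures). The Discussion accepts that participants cannot be blinded.

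**The concern.** In a parallel-group trial, consent and baseline normally come before allocation, so that neither the decision to join nor the baseline answers can depend on the arm. The Control Group wording has them the other way round for one arm, and no other section supplies the usual order.

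Two things would be at stake if the wording were followed. First, a person allocated to control could decline to sign. That person would leave no data, and the controls who remain would no longer be the group that randomisation formed. Second, a person who knew the arm could answer the baseline questionnaires differently. The primary outcome, the Beck Depression Inventory (BDI), is self-reported through an online form, so an assessor who does not know the group gives no protection.

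**Working it through.** The point concerns the order of steps, so the check is a comparison of sections. The document states no figure for it that could be reproduced.

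**1. What each section fixes**

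| Section | Consent and baseline before randomisation? | What it does fix |
|---|---|---|
| Participants | Not stated | Eligibility before randomisation |
| Data Collection and Procedures | Not stated | Verbal agreement, then consent and baseline link; baseline within 2 weeks before the intervention |
| Experimental Group | Not stated | Baseline before training |
| Control Group | Reads as the reverse | Link goes to people described as already allocated |
| Ethics and Dissemination | Not stated | Consent before data collection |

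**2. Orders compatible with the text**

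- *Order A:* eligibility, verbal agreement, randomisation, link, consent, baseline. Every row is satisfied literally, including Control Group.
- *Order B:* eligibility, verbal agreement, link, consent, baseline, randomisation. Every row is satisfied except a literal reading of Control Group. That sentence must then be taken as describing the route of people who are later allocated to control.

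The text therefore permits A, and only a non-literal reading of one sentence gives B. B is the order that protects the trial.

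**3. How order A would enter the analysis, if the arm were known**

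Statistical Analysis plans a two-way repeated-measures ANOVA with pre-to-post and between-group comparisons. Write E for exercise, C for control, 0 for baseline and 1 for week 4. The difference in change is

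D = (E1 − E0) − (C1 − C0).

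If knowing the arm shifts the reported control baseline by δ, C0 becomes C0 + δ, and

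D* = (E1 − E0) − (C1 − C0 − δ) = D + δ.

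The shift passes through one for one. A higher BDI is worse, so a benefit of exercise is a negative D. If controls report worse baseline scores (δ > 0), the benefit is understated; if they report better ones (δ < 0), it is overstated. The same δ enters the contrast of baseline with the 15-day follow-up. A between-group comparison at week 4 alone contains no baseline term and is not affected by δ.

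For refusals, let a fraction p of allocated controls decline, with mean R against S for those who stay. The full control mean is (1 − p)S + pR, so the observed mean S differs from it by −p(R − S). This affects every time point, including week 4 alone.

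**4. Scale**

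Sample Size Calculation gives 56 + 12 = 68 participants. With "patients will be randomized with a 1:1 computer-generated allocation", that is 68 / 2 = 34 per arm. One control lost is 1/34 = 2.9% of the arm. The dropout allowance is 6 per arm, and post-allocation refusals would draw on it if those people are counted as recruited. The document gives no value for p, R − S or δ, so no bias figure follows from it.

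**The case against.** The strongest reply is that the Control Group sentence is a loose restatement of the common step. It closely repeats Data Collection and Procedures (the same link, consent form, baseline form and accompanying video), and the section goes on to trace a control participant from baseline to follow-up. On that reading, allocation to control identifies whose route is described, not when allocation happens. A control-only consent link would also sit awkwardly with assessors who are meant not to know the group. Figures 1 and 2 are described as showing the steps; they were not available here and may give the ordinary order. This reply is plausible and limits the point, but it does not make the sentence right: under it, the sentence still states the wrong order and could be followed.

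A reader might infer more than the text supports:

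- *That Control Group contradicts the general procedure.* It does not do so strictly. Data Collection and Procedures gives no time for randomisation, so both hold under order A.
- *That controls know their arm when they sign or score.* This is not stated. The instruction not to exercise follows the consent and baseline sentence, and the Discussion says only that blinding is impossible, not when the arm is disclosed.
- *That refusals would fall on controls alone.* Under order A the common link would put both arms in the same position. Controls are also invited to take the programme afterwards, which weakens the motive to refuse.
- *That the bias can be sized against the detectable effect.* Sample Size Calculation gives no effect size, so there is no benchmark.
- *That no analysis is safe.* A distorted baseline leaves the unadjusted week-4 comparison untouched, although selective refusal does not.

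**Conclusion.** The point holds as a defect of stated order. The Control Group section reads as consent and baseline after allocation, no other section of the text places them before it, and the exercise arm is described differently. If the wording is followed, post-allocation refusal and arm-aware baseline scores become possible in a trial with unblinded participants and a self-reported primary outcome.

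The resulting bias is a conditional risk, not a demonstrated one. It requires that randomisation really precedes the link and that participants learn, or can infer, their arm before they sign or answer. The document states neither as an operating rule. Size and direction are unknown. If Figures 1 and 2 show baseline before randomisation, what remains is a text correction. It is worth settling before enrolment, because people who refuse leave no data and a baseline cannot be taken again afterwards.

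**What to change.** Reconcile the Participants, Data Collection and Procedures, Experimental Group and Control Group sections by stating one order for both arms:

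1. eligibility confirmed;
2. consent signed;
3. baseline form submitted;
4. randomisation by the researcher who takes no part in the evaluations;
5. disclosure of the arm to the participant.

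Remove the consent and baseline sentence from Control Group, so that this step appears once, in Data Collection and Procedures. In Participants, say that randomisation follows submission of the baseline form. Check that Figures 1 and 2 show the same order.

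The cost is protocol wording and the order in which links are sent. Sample size, instruments and analysis do not change.
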